## Abstract

**Background:**

Individuals with chronic obstructive pulmonary disease (COPD) exhibit reduced levels of physical activity, which are associated with poorer outcomes. The number of clinical trials aiming to promote behavioral changes to increase physical activity in this population has grown; therefore, these trials have yet to produce satisfactory results. An ecological model encompassing individual, social, environmental, and political factors represent a potentially more effective approach to promoting physical activity. While favorable urban environments can positively impact physical activity, specifically tailored environmental interventions for individuals with COPD could enhance their engagement in physical activity. Therefore, the aim of this randomized controlled trial (RCT) study was to analyze the effects of walking in a suggested environment and free walking on physical activity levels in individuals with COPD.

**Methods:**

The environment on physical activity for chronic obstructive disease (EPCOT) is a randomized controlled clinical trial protocol approved by our institution’s Ethics Committee and registered with The Brazilian Registry of Clinical Trials (ReBEC) (https://ensaiosclinicos.gov.br, number RBR-4tfwdhp). This protocol will involve 38 volunteers diagnosed with COPD recruited from the pulmonary physiotherapy and rehabilitation service. The volunteers were randomly divided into two walking groups: an experimental group (ERG) with guidance for walking in a suggested environment and an active control group (ACG) instructed to choose their own routes. The intervention consisted of eight consecutive weeks, with progressive walks carried out 3 to 5 times weekly. The primary outcome will be assessing participants’ physical activity levels. Secondary outcomes will include exercise capacity, quality of life, dyspnea levels, motivation, anxiety, depression, and perceptions of the environment. All assessments will occur before and after the intervention period, aiming to fill a literature gap by investigating the impact of urban environments on COPD-related physical activity. The results may shed light on the importance of environmental factors in promoting physical activity among individuals with COPD, helping to develop more effective interventions.

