### Sample size calculation

The sample size was calculated based on the primary outcome (physical activity) to detect a difference of at least 30 minutes in the weekly average physical activity between groups [33]. The analysis was conducted using G*Power 3.0.10 software (University of Kiel, Kiel, Germany) and considered the following parameters: a two-tailed test, a significance level (alpha) of 5%, and a statistical power of 90%. Based on these criteria, a minimum sample of 36 individuals was required for the study, with 16 participants per group, assuming an effect size of 1.03. To accommodate potential participant attrition and ensure the robustness of the results, an additional 20% was added to the calculated sample size. Therefore, the study will be conducted with a total sample of 44 participants.

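### The abstract plans 38 participants and the sample-size section plans 44; the totals conflict, and 38 cannot reach the stated 90% power even with full retention

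*Protocol article*

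**What the plan says.** The Methods part of the abstract gives the size of the trial as a plain forward statement: "This protocol will involve 38 volunteers diagnosed with COPD". It gives no derivation and does not call 38 an evaluable or minimum number.

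The Sample size calculation section derives a different total. Its inputs are a two-tailed test, alpha of 5%, power of 90% and a standardised effect ("assuming an effect size of 1.03"). It reports that "a minimum sample of 36 individuals was required for the study, with 16 participants per group", then that "an additional 20% was added to the calculated sample size" for attrition, and concludes: "Therefore, the study will be conducted with a total sample of 44 participants".

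The Randomization and allocation section fixes a 1:1 ratio. No section explains 38 or says that one total replaces the other.

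**The concern.** A trial needs one planned enrolment total, and this article gives two that differ by 6 participants. Neither sentence comes from an amendment log, and the mismatch is not detail that an article would leave to a fuller document: one stated number contradicts another.

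The planned sample size is a core pre-specified item, and the article says that it follows SPIRIT. With two published totals, a trial that enrolled 38 and one that enrolled 44 could each be reported as having met its plan. The totals are also not equivalent against the stated power, since 90% is out of reach at 38 and within reach at 44. Many readers will take the size from the abstract, which carries the smaller number with no calculation behind it.

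**Working it through.** **Inputs, all from the Sample size calculation section unless noted.** Standardised effect d = 1.03; two-sided alpha 5%; target power 90%; base figures of 36 in total and 16 per group; 20% added for attrition; total 44. From the abstract: total 38. From Randomization and allocation: 1:1.

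**Step 1: reproduce the plan's inflation.**
- 36 × 1.20 = 43.2, rounded up to 44. This reproduces the sample-size section.
- 2 × 16 = 32, and 32 × 1.20 = 38.4, close to the abstract's 38.

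The base sentence contradicts itself (36 is not 2 × 16), and each published total lies next to one of its two figures. The second match requires rounding down: rounding up gives 39, or 40 for equal groups. Rounding each group to the nearest integer (19.2 to 19, 21.6 to 22) would give both totals. The route is plausible but nowhere stated.

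**Step 2: power at each total.** The method is the exact noncentral t for two independent means. The noncentrality is d × √(n1·n2/(n1+n2)) on n1+n2−2 degrees of freedom, and power is the probability that |t| exceeds the two-sided 5% critical value.

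| Enrolled | Loss | Analysed | Noncentrality | Critical t | Power |
|---|---|---|---|---|---|
| 38 | none | 19 + 19 | 1.03 × √9.5 = 3.175 | 2.028 | 87.1% |
| 38 | 20% (30.4, taken as 30) | 15 + 15 | 1.03 × √7.5 = 2.821 | 2.048 | 77.7% |
| 44 | none | 22 + 22 | 1.03 × √11 = 3.416 | 2.018 | 91.6% |
| 44 | 20% (35.2, taken as 35) | 17 + 18 | 1.03 × √8.743 = 3.046 | 2.035 | 84.0% |

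Rounding the retained numbers up instead gives 79.1% (31 analysed) and 85.1% (36 analysed). The gap between the two totals is 91.6 − 87.1 = 4.5 points with no loss, and 84.0 − 77.7 = 6.3 points after 20% loss.

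**Step 3: the number that gives 90%.**
- 20 + 20 = 40: 88.8%
- 20 + 21 = 41: 89.5%
- 21 + 21 = 42: 90.3% (20 + 22, both losses in one group: 90.2%)

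The stated inputs therefore need 42 evaluable, 21 per group. The total of 38 is below that before any loss. The total of 44 meets it only if no more than 44 − 42 = 2 participants are lost.

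**Step 4: the base figures.** Power is 85.1% at 36 (18 per group) and 80.5% at 32 (16 per group). Neither gives the stated two-sided 90%. Keeping 90% after the attrition allowance would take 42 × 1.2 = 50.4, so 51 enrolled, or 42 / 0.8 = 52.5, so 53 (54 for equal groups).

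**The case against.** The strongest reply is that the Sample size calculation section is the operative text and commits explicitly to 44, while the abstract is only a summary. On that view this is a consistency slip, and most of the power shortfall comes from elsewhere. Part of this stands. Most of the shortfall after attrition comes from the base figure (36 or 32 where 42 is needed), which is a separate error in the sample-size section. What belongs to the 38/44 conflict is 6 participants and about 4.5 to 6 points of power. The reply does not remove the contradiction: the abstract's sentence is a planned total too, and no text ranks one above the other.

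A second fair point is that these are t-test powers, whereas the Statistical analysis section plans mixed linear models using all available data. The percentages check the published calculation on its own terms; they do not predict the power of the eventual analysis.

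A reader might also infer three stronger things that the article does not support:
- That the 36-versus-32 conflict produced the two totals. The arithmetic fits, but 38 is never explained.
- That recruitment could be stopped at whichever total suited the data. No interim look or stopping rule is described, and the Blinding section says that the analyst is blinded.
- That replacing 38 by 44 settles the matter. At 44 the stated 90% is still missed after the 20% loss for which the section itself allows.

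**Conclusion.** The contradiction is established by reading two sentences: 38 and 44 cannot both be the planned total, and a sample size on which the trial relies is therefore wrong as written in one place. At d = 1.03, two-sided 5%, with equal groups and a two-sample t-test, 38 gives at most 87.1% power and so cannot meet the stated 90%. A total of 44 gives 91.6% with full retention and falls below 90% once more than 2 participants are lost. After 20% loss the powers are about 78% and 84%.

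The article states only one power, 90%; the differing powers are implied by the two totals. All the power figures take the effect size of 1.03 as given, since no standard deviation is reported from which to check it. The registry entry was not available, so it is unknown which total, if either, it carries.

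**What to change.** State one enrolment total, with the number per group, in both the abstract and the Sample size calculation section, and in the registry entry if it differs.

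- If the total is 44 (22 per group): change 38 to 44 in the abstract, and restate the power as about 92% with no loss and about 84% after 20% loss.
- If 90% power is to hold after the attrition allowance: start from 42 evaluable (21 per group), recompute the enrolled total (about 51 to 54, depending on how attrition is applied and whether groups are kept equal), and carry it through every place.

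Either way, correct the base sentence at the same time so that the total and the per-group number agree. Keeping 44 costs one number in the abstract and one or two sentences in the sample-size section. The second route also costs 7 to 10 more participants than 44.

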## Introduction

Physical inactivity is a common feature of many chronic diseases, both as a cause and a consequence. The high prevalence of physical inactivity is a problem [1, 2] that contributes to increased morbidity, premature death [3], and healthcare costs [4]. The World Health Organization (WHO) [5], the American College of Sports Medicine [6], and the Physical Activity Guidelines for the Brazilian Population [7] recommend accumulating 150 minutes of moderate physical activity per week or 75 minutes of vigorous physical activity, which translates into health-related benefits. Additionally, accumulating 7,500 to 10,000 steps per day is recommended for adults [8], and accumulating approximately 5,000 steps per day is recommended for older and special populations, such as those with chronic lung diseases [9].

Patients with chronic obstructive pulmonary disease (COPD) perform less physical activity than healthy controls [10, 11]. Existing data show that the amount of time spent walking is lower in patients with COPD than in healthy individuals of the same age [12–14]. Associations between physical activity and the clinical characteristics of COPD patients, such as disease severity, comorbidities, exacerbations, and behavioral factors, have also been observed [15]. Prospective longitudinal studies have shown an association between low levels of physical activity and an increased number of exacerbations, risk of hospitalization, and all-cause mortality in COPD patients [16, 17].

Studies have focused on testing the effectiveness of interventions such as pulmonary rehabilitation programs, pharmacological treatment, oxygen therapy, and behavioral interventions for increasing physical activity in COPD patients [18, 19]. However, these interventions have primarily been designed to target individual factors such as limiting symptoms, physical capacity, and overall health status, which have not resulted in lasting lifestyle changes for this population [19]. On the other hand, physical activity depends on various factors, including biological, behavioral, and genetic factors, as well as social, environmental, cultural, and public policy factors.

The ecological model of physical activity adopts a comprehensive perspective to understand inactive behavior, recognizing the influence of social and environmental factors, including external health components such as urban planning, transportation systems, squares, parks, and bike paths [20]. The urban environment plays a significant role in promoting physical activity, as living in cities that support exercise can help residents achieve approximately 45–59% of the recommended weekly guidelines for 150 minutes of physical activity [21].

Studies [22, 23] highlight that social, cultural, historical, and economic variations lead to distinct behaviors in population groups, reflected in people’s lifestyles influenced by family experiences, educational settings, and specific regional contexts. Therefore, adherence to specific behavioral patterns results from complex interactions between individual and contextual factors. "Walkability" is a concept that assesses the suitability of routes for walking and active transportation [24]. This subject has garnered growing attention in health research, spanning diverse populations ranging from older [25] to children to adolescents [26] and addressing various health conditions, such as diabetes risk [27], obesity [27, 28], and cardiovascular risk [29–31]. These investigations offer valuable insights into the influence of urban infrastructure on physical behavior and overall health. Walkability employs a combination of quantitative and qualitative methods to improve the allure and safety of streets and neighborhoods, ultimately fostering pedestrian mobility.

Three studies [32–34] addressed different strategies to promote physical activity in COPD patients. The first investigated the effectiveness of "Urban Training", revealing an increase in physical activity after 12 months [32]. The second study implemented urban walking circuits following rehabilitation in COPD patients, resulting in an average increase of 32.4 minutes of physical activity per day in the urban circuit group compared to the control group [33]. The third study focused on low-income and ethnically diverse adults in the U.S. introduced the "Peer Empowerment Program 4 Physical Activity" to promote physical activity among adults older than 50 years, highlighting the potential of peer-led approaches in community programs [34]. These trials highlight the importance of using predefined and contextualized routes to promote physical activity. However, urban circuits were not personalized in these studies according to the best walkability and participant preference.

Based on these premises, we hypothesize that a suggested route of better walkability, tailored and selected according to individual preferences, could encourage individuals with COPD to increase and maintain walking physical activity compared to a control group with free walking. Therefore, the aim of this randomized controlled trial (RCT) study was to analyze the effects of walking in a suggested environment and free walking on physical activity levels in individuals with COPD.

### Study design

The environment on physical activity for chronic obstructive disease (EPCOT) is a protocol for a parallel, two-group, randomized controlled trial that used concealed allocation with a 1:1 ratio and intention-to-treat analysis designed by independent investigators. The trial was registered at The Brazilian Registry of Clinical Trials (ReBEC) (https://ensaiosclinicos.gov.br, number RBR-4tfwdhp update on 04/12/2024) and follows the guidelines of the *Standard Protocol Items*: *Recommendations for Interventional Trials (SPIRIT)* [35, 36] (S1 Appendix).

The study protocol conformed to the ethical guidelines of the Declaration of Helsinki and was approved by the Research Ethics Committee of University Hospital of the Federal University of Juiz de Fora/MG (Approval Number: #5.889.099, on March 29, 2023). Written informed consent will be obtained from all participants.

Eligible participants received detailed information about the study’s objectives, risks, and benefits from the assessors. After reading and signing the informed consent form (S2 and S3 Appendices), participants provided consent to participate in the study, as established by Resolution 580/2018 of the National Health Council of Brazil. To ensure the privacy and confidentiality of the collected data, appropriate measures will be taken by the entire research team. The principal investigator safeguarded the information’s security by using codes instead of participants’ identifying data and controlling access to electronic files through a unique password. The data collected and analyzed by this Project will be disseminated at congresses and through international peer-reviewed journals and will not be reported in any of the forms of dissemination in this study.

Random sampling will form two groups: an experimental group (ERG), which will engage in physical activity through walking on suggested routes with better walkability, and an active control group (ACG), which will be instructed to choose their own routes. Previously trained researchers will carry out the study. Primary and secondary outcome measures will be assessed two days, 48 hours apart, to prevent participant exhaustion. After an 8-week intervention period, reassessment will be performed (Fig 1).

**Fig 1 pone.0306045.g001:**
[figure not shown]
SPIRIT diagram. The figure details the timing of enrollment activities, intervention allocation, and assessments of outcomes over the course of the clinical trial. SPIRIT, Standard Protocol Items: Recommendations for Interventional Trials.

### Sample size calculation

The sample size was calculated based on the primary outcome (physical activity) to detect a difference of at least 30 minutes in the weekly average physical activity between groups [33]. The analysis was conducted using G*Power 3.0.10 software (University of Kiel, Kiel, Germany) and considered the following parameters: a two-tailed test, a significance level (alpha) of 5%, and a statistical power of 90%. Based on these criteria, a minimum sample of 36 individuals was required for the study, with 16 participants per group, assuming an effect size of 1.03. To accommodate potential participant attrition and ensure the robustness of the results, an additional 20% was added to the calculated sample size. Therefore, the study will be conducted with a total sample of 44 participants.

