### Intervention

Participants allocated to the experimental group will receive personalized and individual routes of better walkability, developed by an architect and urban planner through a virtual urban environmental analysis using the Microscale Audit of Pedestrian Streets (MAPS) [40], to collect audit data on the pedestrian environment and walkability in neighborhoods. The analysis will be performed through a geographical map based on satellite positioning from the participant’s residence. The architect and urban planner will conduct an interview with the participant to detect information that is not identified through virtual urban environmental analysis and will present the suggested routes combined with the participant’s preferences, choices, and acceptance. Participants in this group will receive 5 personalized circuits, with durations of approximately 15 minutes, 20 minutes, 30 minutes, 40 minutes, and 50 minutes, along with distances in kilometers. Each route includes a marked map of the path, a description of the start and end, and information about nearby cultural attractions or commercial areas. On the other hand, the control group will receive only guidance for walking without a specific route suggestion, allowing each participant to freely choose their walking path. The intervention period will last for 8 weeks, and participants will be advised to walk 3 to 5 times a week. The progression will follow the following schedule: in the first week, 15 minutes/day; in the second week, 20 minutes/day; in the third week, 30 minutes/day; in the fourth week, 40 minutes/day; and in the fifth week, 50 minutes/day until the eighth week.

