### Primary outcomes

An objective evaluation of participants’ daily physical activity levels will be conducted using the Actigraph GT3X^®^ accelerometer (Actigraph LLC, USA). This physical activity monitoring tool has been validated and found to be reliable for use in individuals with COPD [47]. The level of physical activity will be assessed by measuring the amount of time spent in minutes in light, moderate, and vigorous activity categories, as well as the total time, in addition to the daily step count and indicators of energy expenditure [10]. The collected data will be processed, recorded, and stored in the device’s internal memory, generating a report that will be analyzed on a computer using the specific ActiLife 6 software (Actigraph LLC, Pensacola, FL, USA) [48].

Before commencing accelerometer use, participants received instructions on how the device functions and its purpose. An elastic strap was worn to secure the accelerometer at the line of the iliac crest of the dominant lower limb. The accelerometer was worn continuously for a period of 7 consecutive days, with removal occurring only during bathing, water-related activities, and sleep. The device’s small size and minimal dimensions ensure comfort during use. Each participant will receive the accelerometer along with a manual containing information and instructions on the proper use of the device, as well as a diary recording the day of the week and the times the device is attached and removed. After the usage period, evaluators collected the device for data analysis.

The stored data will be analyzed using ActiLife 6 software (Actigraph LLC, Pensacola, FL, USA). The data will be collected at a frequency of 30 Hz and analyzed in 60-second epochs [49]. A day of data was considered valid if there was a minimum of 10 hours of use during 24 hours (from 0:00 to 23:59) [48]. The data from the first and last days were discarded, with a minimum of four days included in the analysis; at least one weekend day was included [50, 51].

The data analysis will be limited to waking hours, excluding any records during sleep. To calculate the minutes spent on moderate and vigorous activities per week, the data from all valid days were summed, adjusted for the total number of valid days, and multiplied to obtain the individual weekly average.

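### The target difference behind the power statement is 30 minutes in a weekly average, but the study cited for it is reported as 32.4 minutes per day, so the unit and the basis of d = 1.03 need restating

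*Protocol article*

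**What the plan says.** The Sample size calculation section states that the trial is sized "to detect a difference of at least 30 minutes in the weekly average physical activity between groups", with reference 33 as the source. The test settings are "a two-tailed test, a significance level (alpha) of 5%, and a statistical power of 90" per cent, and the result is given as "a minimum sample of 36 individuals was required for the study, with 16 participants per group, assuming an effect size of 1.03". Adding 20% for attrition brings the total to 44. The section prints no SD.

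The Introduction describes the same reference 33 as "resulting in an average increase of 32.4 minutes of physical activity per day in the urban circuit group compared to the control group".

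The Primary outcomes section gives its calculation rule in weekly terms: "To calculate the minutes spent on moderate and vigorous activities per week", valid days are summed and scaled, and the result is called the individual's weekly average. That section also lists light and total time, steps and energy expenditure.

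Under Intervention, "participants will be advised to walk 3 to 5 times a week", with walks rising to 50 minutes from week five to week eight. No other frequency or duration is given for the control arm. The arms differ in whether a route is suggested. The pedometer, diary, booklet, education sessions and calls go to both.

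**The concern.** The target difference and its cited source are in different time units, and the outcome section leans towards the weekly one. Taken literally, the trial aims at a difference about one seventh the size of the effect it cites. If a daily figure was meant, the sample size wording clashes with the scale on which the outcome is built.

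This matters because the paragraph holds the only power statement in the article. A reader faced with a null result could not tell whether the trial was designed to detect about 4 or about 30 minutes per day. Each reading also raises its own question: on the weekly one, whether the implied SD is realistic; on the daily one, whether so large a difference can be expected when the control arm gets the same walking advice and support.

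**Working it through.** **Inputs.** Difference 30 minutes, d = 1.03, two-sided alpha 0.05, power 90%, 36 total or 16 per group, 44 after the 20% addition (Sample size calculation). Cited effect 32.4 min/day (Introduction). Three to five walks a week of 50 minutes in weeks 5 to 8 (Intervention). Allocation 1:1 (Study design). Power is from the noncentral t distribution for an unadjusted two-sample comparison.

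**1. The plan's own figure.** At d = 1.03:

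| Evaluable per arm | Power |
|---|---|
| 16 | 80.5% |
| 18 | 85.1% |
| 21 | 90.3% |
| 22 | 91.6% |

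Ninety per cent needs 21 per arm, 42 in total, so the stated 36 is not reproduced; nor is 16 per group, which makes 32. The 44 follows from 36 × 1.2 = 43.2, rounded up to an even number. If 20% of 44 are lost, 44 × 0.8 = 35.2, about 35 remain (17 and 18), and power at d = 1.03 is 84.0%.

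**2. Implied SD.** SD = difference / d = 30 / 1.03 = 29.1, in whichever unit the 30 minutes carries.

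**3. Weekly reading.**
- Target per day: 30 / 7 = 4.3 min/day. Share of the cited effect: 4.3 / 32.4 = 13%.
- Implied SD: 29.1 min/week, or 29.1 / 7 = 4.2 min/day.
- For scale, advised walking in weeks 5 to 8 runs from 3 × 50 = 150 to 5 × 50 = 250 min/week, a range of 100 min/week among people who all follow the advice. If they split evenly over 3, 4 and 5 walks (an assumption), the SD of 150, 200 and 250 is 40.8.
- Power for a 30 min/week difference under assumed SDs:

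| SD (min/week) | d = 30/SD | 22 per arm | 17 and 18 |
|---|---|---|---|
| 29.1 (implied) | 1.03 | 92% | 84% |
| 40 | 0.75 | 68% | 58% |
| 40.8 | 0.73 | 66% | 56% |
| 60 | 0.50 | 37% | 30% |
| 80 | 0.375 | 23% | 19% |

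Only the first row rests on the article's own d.

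**4. Daily reading.**
- Target per week: 30 × 7 = 210 min/week, which is 210 / 250 = 84% of the maximum advised in either arm.
- Two arms that both follow the advice in weeks 5 to 8 can differ in prescribed walking by at most 250 − 150 = 100 min/week, or 100 / 7 = 14.3 min/day, about half the target.

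**The case against.** The weekly wording may simply mean daily minutes averaged over the monitored week. The closeness of 30 to 32.4 supports this, and on that reading there is no sevenfold error, only loose wording. This stands: the primary outcome section favours minutes per week but does not settle the matter.

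Three stronger readings are tempting, and the documents support none of them.

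- *That d = 1.03 cannot be believed on either reading because both arms share a walking prescription.* On the weekly reading, 30 minutes is less than one 50-minute walk, and a range of three to five walks easily allows it. The doubt there rests on the SD alone. On the daily reading the prescription makes the target look large but does not rule it out.
- *That true power is far below 90%.* The SDs of 40, 60 and 80 are assumptions, and 40.8 is the spread of three advised totals, not of accelerometer-measured activity. The planned mixed model on before-and-after data may also do better than an unadjusted t-test. The low power figures are conditional.
- *That a daily target would cap the control arm at 250 − 210 = 40 min/week of walking.* This treats advised walking as a ceiling and as all of the measured activity. The accelerometer records all waking hours, and reassessment follows the 8-week period, so the week-eight advice need not apply in the measurement week.

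It is also fair to say that the SD and the derivation of d may stand in a fuller protocol or analysis plan, and that the control condition of the cited study is not described, so transfer of its effect cannot be tested here. These points limit the finding to what the article states. The unit conflict remains.

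**Conclusion.** The point holds as a conflict of units and an unsupported link to the cited effect. Either the target is about one seventh of the effect cited for it, or it is a daily figure worded in a way that clashes with the weekly outcome scale. The article does not say which.

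The implied 29.1 min/week looks small beside a 100 min/week range of advised walking, but the documents give no outcome SD against which to test it. A difference of 30 min/day would be more than twice the largest gap in prescribed walking between two adherent arms, so it needs a justification specific to a contrast in route guidance alone.

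One part needs no assumed SD: at the stated d, two-sided 90% power requires 21 evaluable per arm, and about 35 evaluable in total gives 84%. That figure assumes 20% attrition and an unadjusted two-sample t-test. The power statement therefore needs restating whichever unit was intended.

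**What to change.** Rewrite the sample size paragraph so that it:

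1. names the primary activity variable and states the target difference in that variable's unit;
2. corrects the weekly wording if the 32.4 min/day effect was the basis, or explains why a much smaller weekly target was chosen if it was not;
3. gives the SD behind d = 1.03 and its source;
4. justifies the difference for an active control with the same walking advice and support;
5. restates power for 44 enrolled and about 35 evaluable over a plausible range of SDs, using the planned analysis if baseline adjustment is to be credited, and reconciles the 36 and the 16 per group with the result.

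The cost is one paragraph. The stated power will look less favourable, and no extra patients are needed to make the correction.

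### The evaluable numbers given for 90% power, 36 in total and 16 per group, disagree with each other, and neither follows from the stated inputs, which need 42

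*Protocol article*

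**What the plan says.** The Sample size calculation section of the protocol article bases the trial's size on the primary outcome, physical activity, and aims "to detect a difference of at least 30 minutes in the weekly average physical activity between groups". It names G*Power, "a two-tailed test", and "a significance level (alpha) of 5%, and a statistical power of 90" per cent. The result is given as "a minimum sample of 36 individuals was required for the study, with 16 participants per group, assuming an effect size of 1.03". For attrition, "an additional 20% was added to the calculated sample size", which leads to a total of 44.

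The Study design and the Randomization and allocation sections specify two groups at 1:1. The Abstract (Methods) gives the trial's size as 38 volunteers. The Statistical analysis section plans mixed linear models for the primary and secondary outcomes. The article gives no standard deviation and no baseline/follow-up correlation.

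**The concern.** Two equal groups of 16 make 32, so the sentence gives two different minimum samples. Both also look small for 90% power at a standardised difference of 1.03.

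This paragraph is the only justification for the trial's size. If the stated power does not belong to the stated numbers, readers cannot tell how much weight a null result can bear. The effect assumed is already large, so any shortfall means that only a still larger effect would be detected with 90% power. The 38 in the Abstract also leaves it unclear which total any corrected statement should refer to.

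**Working it through.** **Inputs from the Sample size calculation section.** Two-sided alpha 0.05, power 0.90, effect size 1.03, stated minimum 36 (also 16 per group), 20% added, total 44. Allocation is 1:1 (Randomization and allocation section). The Abstract's total is 38.

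**Assumption.** The effect size is Cohen's d and the test is the independent-groups t-test. The article states neither, but a comparison of two group means with a single effect size points to them. On this reading the implied SD is 30/1.03 = 29.1 minutes.

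**Formula.** With df = n1 + n2 − 2 and noncentrality λ = d·√[n1·n2/(n1 + n2)], power is the probability that a noncentral t(df, λ) exceeds the two-sided 5% critical value (the opposite tail is negligible here).

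**Step 1: the plan's own figures.** 2 × 16 = 32, not 36.
- 16 per group: λ = 1.03·√8 = 2.913, df 30, critical value 2.042, power 80.5%.
- 18 per group (36): λ = 1.03·√9 = 3.090, df 34, critical value 2.032, power 85.1%.
- 16 and 20 (36, unequal): power 84.7%.

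The stated 90% is not reproduced. Sixteen per group is the smallest number that reaches 80% power, and 18 per group the smallest that reaches 85%.

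**Step 2: what the inputs require.**
- 20 per group (40): 88.8%.
- 20 and 21 (41): 89.5%.
- 21 per group (42): λ = 1.03·√10.5 = 3.338, df 40, power 90.3%.

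The requirement is 42 evaluable. The normal approximation gives 20 per group, or 40, which also matches neither stated figure.

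**Step 3: other readings.**
- A one-sided 5% test at 90% needs 17 per group, or 34. That is neither 32 nor 36, and it contradicts the stated two-tailed test.
- A Wilcoxon-Mann-Whitney test needs 22 per group (relative efficiency 0.955) to 25 per group (0.864), so the gap widens.

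**Step 4: enrolled totals.** The section's own step is 36 × 1.2 = 43.2, rounded up to 44 for equal arms.

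| Enrolled | Loss | Evaluable | Power at d = 1.03 |
|---|---|---|---|
| 44 | none | 44 | 91.6% |
| 44 | 2 participants (4.5%) | 42 | 90.3% |
| 44 | 20% (44 × 0.8 = 35.2) | about 35 (17 and 18) | 84.0% |
| 38 | none | 38 | 87.1% |
| 38 | 20% (38 × 0.8 = 30.4) | about 30 | 77.7% |

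**Step 5: effect detectable with 90% power.** d = 1.11 with 36 evaluable, 1.13 with 35 and 1.18 with 32.

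**Step 6: possible origin of the totals.** 32 × 1.2 = 38.4 lies close to the Abstract's 38, and 36 × 1.2 = 43.2 leads to 44. Two calculations may have been mixed. This is an inference from the arithmetic; the article does not say so.

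**The case against.** **Enrolment of 44 covers the requirement.** This largely stands if losses are small: 44 gives 91.6%, and 90% is kept down to 42 evaluable. A reader might infer from the mismatch that the trial cannot deliver 90% power at all, and the article does not support that. With 44 enrolled and losses from 0 to 20%, type II error runs from about 8% to 16%. The 20% figure that goes with 32 evaluable would need a 27% loss (12 of 44), more than the plan allows for.

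**The attrition step is consistent.** This also stands. A reader might count the 20% allowance as another disagreeing figure, but 36 plus 20%, rounded up to even arms, is 44, and the article does not claim that 36 remain after a 20% loss. Dividing by 0.8 would give 45, one more. It is a side remark that a 20% loss from 44 leaves about 35, just under the stated 36.

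**The test is inferred.** This is true and has to be declared. The alternatives tried that keep the two-tailed test and use no baseline data also give neither 36 nor 32.

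**The planned mixed model may use baseline data.** If d is on the follow-up SD, the effective effect size is d/√(1 − r²). A baseline/follow-up correlation r of about 0.38 would bring 36 evaluable to 90%, and r = 0.49 would do so for 32. With r = 0.5 and 35 evaluable, 1.03/√0.75 = 1.19 and power is about 93%. This limits the practical consequence. It does not rescue the stated calculation, which gives no correlation and is not linked to the model.

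**Conclusion.** The sample size paragraph is wrong as written. Its two minimum samples contradict each other, which needs no assumption to see. Under Cohen's d and an independent-groups t-test at 1:1, the stated inputs require 42 evaluable; the two stated figures carry 85.1% (36) and 80.5% (32).

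The power shortfall for the trial itself is conditional. With 44 enrolled it appears once more than two participants are lost, and it reaches 6 points (84.0% against 90%) at the 20% loss planned for. If the Abstract's 38 is the true total, 90% is missed even with complete data. These power figures assume no gain from baseline adjustment.

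The text must be corrected, because the 90% claim is false for both stated evaluable numbers. The consequence is modest if 44 is the real target.

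**What to change.** 1. Check what was entered into G*Power (test, power, effect size, resulting n) and reconcile 32, 36, 38 and 44 across the Abstract and the Sample size calculation section.
2. Name the test and say what the effect size of 1.03 measures.
3. Restate power for the confirmed total.
   - If 44 is confirmed: *44 randomised (22 per group); with 20% loss, about 35 evaluable give 84% power for d = 1.03, or 90% power for d = 1.13; 42 evaluable are needed for 90% power at d = 1.03.* Correct the Abstract to match.
   - If 38 is confirmed: state 87% power with no loss and about 78% with 30 evaluable, and correct the 44.
4. If the calculation relies on baseline adjustment in the mixed model, state the assumed baseline/follow-up correlation and the SD on which d is based.

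The cost is one rewritten paragraph, one corrected number elsewhere and a less favourable power statement. No participants beyond the planned number are needed, and the analysis does not change.
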